### Primary outcomes and secondary outcomes

The main study outcome is the number of wetting accidents per week after 3 months of urotherapy. Secondary outcomes are number of per-post wetting accidents classified further according to the ICCS standards in complete response (100% reduction of complaints), partial response (50-99% reduction), and no response (less than 50% reduction) [14]. Furthermore, magnitude of the placebo-effect contribution (SHAM versus control) will be assessed next to subjective improvement of symptoms according to child and parents, number of wetting accidents per week during follow-up 6 months after baseline, cost effectiveness, and change in FVC parameters (average, minimum, maximum voided volumes corrected for bladder capacity for age (EBC) between baseline (T0), after 3 months (T3), and after 6 months (T6). Change in disease specific quality of life as measured by the PINQ is also compared between T0, T3, and T6.

Other objectives include adherence to urotherapy and adherence of wearing the SENS-U/SHAM, patient experiences of user friendliness/(dis)comfort of the SENS-U/SHAM device, occurrence of urinary tract infections and constipation, and uroflowmetry curves.

Adherence to urotherapy is defined as number of failed contact moments/number of expected contact moments during the 3 months training. The SHAM and SENS-U measure the number of days actually worn. Adherence of wearing the SENS-U/SHAM is measured as a proportion (number of days not worn/total number of days used in training).

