**Methods/design:**

This is a multi-center clinical superiority parallel-group randomized controlled trial including a total of 480 children. Participants between 6 and 16 years of age with functional DUI in which urotherapy is offered as the next treatment of choice are eligible. Four centers, two academic hospitals, and two general care (peripheral) centers are participating. Participants will be randomized at a 1:1:1 ratio into three groups: urotherapy (care as usual), urotherapy with the SENS-U added for 3 consecutive weeks throughout the training, or urotherapy with a SHAM device for 3 weeks. The primary outcome is number of wetting accidents per week after 3 months of training, compared between the SENS-U and the SHAM device. The magnitude of the placebo effect will be assessed by comparing the results of the SHAM group versus the control (care as usual) group.

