### Interventions for subjects randomized to urotherapy + SENS-U or urotherapy + SHAM

Urotherapy is given as mentioned previously and the same for all participating subjects, including the PROMS. In addition the SENS-U or SHAM is added. A health care provider will administer and install the device and explain parents and child how to apply and use the device. The SENS-U is used to provide biofeedback which teaches the child the feeling that corresponds with the feeling of a full bladder. The alarm can be personalized by adjusting the percentage of bladder filling at which it sends an alarm, based on the child’s own bladder capacity and FVC. The SENS-U is able to monitor the natural bladder filling during regular activity in children, as required for application in urotherapy.

The feeling of a device on the children’s belly could increase awareness of their bladder and might induce a placebo effect. Therefore, we included a placebo group, wearing a SHAM device that alerts independent of bladder filling at a set interval. The SHAM device resembles the traditional timer watch which is currently often used in urotherapy [13]. Therefore, it is not considered an extra burden for children to wear a SHAM device. The SHAM and accompanying instructions for use are identical to the SENS-U. The interval between alarms is randomly chosen between 2 and 3 h to appear realistic. To establish a good learning effect but preventing any dependency of the child on a device, either the SENS-U or SHAM will be worn for a total of 21 consecutive days in the overall 3 months of training. After the period of 21 days, an evaluation is done addressing items like comfort and user friendliness. Before the start of the study, all involved health care professionals are instructed about the use of the SENS-U/ SHAM. The project leader will coordinate instructions and training on the research protocol for the SENS-U study. An overview of the study procedures are shown in Table 1.

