### Sample size

The sample size calculation is based on detecting a difference between the intervention (SENS-U) group and the placebo (SHAM) group at the 3 month endpoint on the primary outcome number of wetting accidents per week. Following the ICCS guidelines, most published studies categorize the number of “wetting accidents per week” in three categories (complete response, partial response, no response) [14]. Information about the initial data used for the categorization (i.e., the number of wetting accidents) is seldom available. Therefore, our sample size calculation is based on a Fisher’s exact test with the known proportions. This will give a slight overestimation of the necessary sample size when analyzing wetting accidents per week, since this latter variable has more variance.

In this calculation, we assume the SHAM condition to be comparable to urotherapy using currently existing wearable alarm treatments (timer watch, pants alarm) [13, 15]. Success rate vary between 53 and 74%, depending on type of referral center [16, 17]. Since this study includes first- to third-line centers, we use an average success rate of 64% to be the estimate success rate of the SHAM condition in our sample size calculation. In addition, we expect at least a 15% additional effect in the intervention (SENS-U) group, based on current clinical experiences with the SENS-U [12].

With a Fisher’s exact test for two independent proportions, one-sided *a* = 0.05, power = 0.80, 64% success in the SHAM group, and 79% success in the SENS-U group, 124 children per group are needed. The one-sided alpha will provide a slight underestimation of the sample size. Given the previous assumption that our sample size calculation result in slight overestimation of the sample size, we presume that the overestimation and underestimation will cancel each other out. With 23% lost to follow-up, we need 160 children per group, 480 children in total.

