This study has several strengths. Children from first-, second-, and third-line centers throughout several areas in the Netherlands are included to represent the overall group of children with functional DUI as much as possible. It is one of the few studies that will give a better insight in adherence of alarm systems used, as current literature concerning this element is sparse. As previously mentioned, trials studying not only the effect but also the cost-effectiveness of certain treatment modalities are essential as overall health costs are increasing. The study also has some potential limitations. Complete blinding of subjects is only possible for those allocated to either a SENS-U or SHAM device. Those allocated to urotherapy alone are not blinded (nor is the urotherapist in this case). As cognitive behavioral treatment is an important part of training, motivation in those not randomized to any type of device might be impaired. Potential discomfort or social embarrassment in those allocated to a SENS-U or SHAM might lead to less adherence and subsequent impact on outcome as well.

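### SHAM versus care as usual is labelled the placebo effect, but the SHAM gives timed alarms like an existing treatment tool, so the contrast cannot isolate a placebo effect

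*Protocol article*

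**What the plan says.** The article fixes the interpretation of one secondary contrast in two places. Under Primary outcomes and secondary outcomes, the "magnitude of the placebo-effect contribution (SHAM versus control) will be assessed". The Abstract (Methods/design) is plainer: "The magnitude of the placebo effect will be assessed by comparing the results of the SHAM group versus the control (care as usual) group".

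The section on interventions for the two device arms gives the reasoning. The feel of a device on the belly "could increase awareness of their bladder and might induce a placebo effect", so a placebo group is included, "wearing a SHAM device that alerts independent of bladder filling at a set interval". On the timing: "The interval between alarms is randomly chosen between 2 and 3 h to appear realistic". The same paragraph adds: "The SHAM device resembles the traditional timer watch which is currently often used in urotherapy".

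The Sample size section takes the likeness further: "we assume the SHAM condition to be comparable to urotherapy using currently existing wearable alarm treatments (timer watch, pants alarm"). It sets SHAM success at 64%.

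On blinding, the Randomization section covers SENS-U versus SHAM only. The Discussion says that children on urotherapy alone, and their urotherapist, are not blinded, and that "motivation in those not randomized to any type of device might be impaired".

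**The concern.** The article uses the SHAM arm in two incompatible ways. When the trial is sized, the arm stands in for alarm treatment as now practised. When the result is read, it stands for placebo. The Background describes interval alarms as telling the child to go to the toilet and lists alarm interventions among the usual tools of urotherapy. A device that prompts every 2 to 3 hours may work through that prompting, and this is not the mechanism the article gives for the placebo effect, which is awareness from wearing something.

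If the plan is followed as written, any benefit of timed prompting will be published as placebo. That matters all the more because the article presents the trial as the first to study the effect and cost-effectiveness of alarm interventions added to urotherapy. Of the contrasts it names, SHAM versus care as usual is the closest to a timer-type alarm added to urotherapy.

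**Working it through.** **The plan's own figure.** The only related calculation is the sample size for SENS-U versus SHAM: 64% versus 79%, one-sided alpha 0.05, power 0.80.

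- Mean proportion: (0.64 + 0.79)/2 = 0.715.
- Without continuity correction: n = [1.645·√(2·0.715·0.285) + 0.842·√(0.64·0.36 + 0.79·0.21)]² / 0.15² = 110.9, so 111.
- With continuity correction: n = (110.9/4)·[1 + √(1 + 4/(110.9·0.15))]² = 123.9, so 124 per group, as stated.
- Exact one-sided Fisher power at 124 per group is 0.806.
- Allowing for 23% loss: 124/0.77 = 161.04, which rounds up to 162 against the stated 160, a trivial gap.

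The figure reproduces and has no bearing on this point, which concerns what a different contrast measures.

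**What each arm contains.** All arms receive urotherapy. What differs, from the sections cited above:

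| Component | Care as usual | SHAM | SENS-U |
|---|---|---|---|
| Device worn, with expectation (W) | no | yes | yes |
| Timed prompts (T) | not stated | yes | no |
| Bladder-triggered prompts (B) | no | no | yes |
| Child knows there is no device (C) | yes | no | no |

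Write each contrast as a gain in continence and, for illustration only, let the components add. Assume no timers in the control arm. Let C be the gap caused by demotivation of controls, and let W include any loss from discomfort or poor adherence.

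- SHAM − control = T + W + C
- SENS-U − SHAM = B − T (W cancels if the blind holds)
- SENS-U − control = B + W + C

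The third line is the sum of the first two, so three arms give two independent contrasts for four unknowns. W, the placebo effect as the article describes it, cannot be recovered from them. SHAM − control equals W only if T = 0 and C = 0. The Sample size section's assumption about existing alarm treatments sits badly with the first condition, and the Discussion doubts the second.

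**Direction.** T > 0 or C > 0 would make the contrast larger than W. Timer or alarm use among control children would shrink it. The Abstract says alarm therapy can be part of urotherapy, and the article does not say whether controls may have it. The Discussion also expects possible discomfort and lower adherence among device wearers, which would reduce the contrast too. The net direction is therefore open.

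**The case against.** The strongest reply has four parts.

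- **The SHAM is a fair placebo for the claimed mechanism.** SENS-U is meant to teach bladder sensation, and the article says existing alarms do not. The alarms also make the SHAM credible and protect the blind. This stands for SENS-U versus SHAM. A reader might infer that the primary comparison is misdescribed or invalid, but the article openly describes the SHAM as alarming independently of bladder filling, so its content is clear. The reply does not help SHAM versus care as usual, where the timed prompts are part of the difference being called placebo.

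- **An unblinded no-device arm is unavoidable, and disclosed.** This is true, and it is not a fault of design. What remains is that the disclosure is never connected to the placebo estimate.

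- **The size cannot be given.** A reader might set 64% for SHAM against the 54% for urotherapy in the Background and conclude that 10 points would be mislabelled. The documents do not support this. The 54% is a within-one-year pooled rate, never assigned to the control arm and not shown to be free of alarms. The sources cited for the SHAM success range differ from those cited for its likeness to alarms. Over the Background's 40 to 70% range for urotherapy, the gap runs from 64 − 40 = +24 to 64 − 70 = −6 points.

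- **Pairwise contrasts can be left to an analysis plan.** A reader might infer that SENS-U versus care as usual will go unexamined. The planned mixed model compares all three groups and can supply it, and an unseen analysis plan may name it. Its absence here is not a finding by itself.

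**Conclusion.** The label is wrong on the article's own description. SHAM versus care as usual estimates the combined effect of timed prompting, wearing a device with its expectation, and open-label allocation of controls. It does not estimate the magnitude of a placebo effect, and no other contrast in the design can extract one.

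This rests on reading the comparison with timer watches and alarm treatments at face value. The article says the SHAM resembles and is comparable to these; it does not show that timed prompting works. If prompting had no effect and controls were not demotivated, the label would do little harm, but the trial cannot establish either condition.

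Neither the size nor the direction of the error can be given from the document. The consequence is confined to the interpretation of one secondary contrast. Randomization, data collection, the primary test and the sample size are untouched. The point still deserves correction before results are known, because it decides what the trial may conclude about timed alarms.

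**What to change.** 1. In the Abstract and in the outcomes section, replace the reference to the size of the placebo effect with: *combined effect of wearing a timed-alarm device, including expectation, versus open-label care as usual*. State that no placebo effect will be concluded from this contrast.
2. Where the Discussion mentions impaired motivation in unblinded controls and discomfort among device wearers, add that both bear on this contrast, in opposite directions.
3. As a sensible addition, name SENS-U plus urotherapy versus urotherapy alone as a secondary contrast from the three-group model already planned, and as a comparison in the cost-effectiveness analysis. The aim concerns adding SENS-U to urotherapy, and the Cost-effectiveness analysis section does not state its comparator outright.

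The cost is a few sentences and one further contrast from a model that will be fitted anyway. No patients, visits or data are added, and the primary comparison stays as it is.

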### Sample size

The sample size calculation is based on detecting a difference between the intervention (SENS-U) group and the placebo (SHAM) group at the 3 month endpoint on the primary outcome number of wetting accidents per week. Following the ICCS guidelines, most published studies categorize the number of “wetting accidents per week” in three categories (complete response, partial response, no response) [14]. Information about the initial data used for the categorization (i.e., the number of wetting accidents) is seldom available. Therefore, our sample size calculation is based on a Fisher’s exact test with the known proportions. This will give a slight overestimation of the necessary sample size when analyzing wetting accidents per week, since this latter variable has more variance.

In this calculation, we assume the SHAM condition to be comparable to urotherapy using currently existing wearable alarm treatments (timer watch, pants alarm) [13, 15]. Success rate vary between 53 and 74%, depending on type of referral center [16, 17]. Since this study includes first- to third-line centers, we use an average success rate of 64% to be the estimate success rate of the SHAM condition in our sample size calculation. In addition, we expect at least a 15% additional effect in the intervention (SENS-U) group, based on current clinical experiences with the SENS-U [12].

With a Fisher’s exact test for two independent proportions, one-sided *a* = 0.05, power = 0.80, 64% success in the SHAM group, and 79% success in the SENS-U group, 124 children per group are needed. The one-sided alpha will provide a slight underestimation of the sample size. Given the previous assumption that our sample size calculation result in slight overestimation of the sample size, we presume that the overestimation and underestimation will cancel each other out. With 23% lost to follow-up, we need 160 children per group, 480 children in total.

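### The 80% power holds only for a one-sided 5% test; at two-sided 5% it is about 70%, and the presumed offset from analysing counts is unsupported

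*Protocol article*

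**What the plan says.** The Sample size section bases the calculation on "detecting a difference between the intervention (SENS-U) group and the placebo (SHAM) group at the 3 month endpoint", with wetting accidents per week as the primary outcome. Because published studies seldom report the counts themselves, it works with success proportions instead: "With a Fisher’s exact test for two independent proportions, one-sided *a* = 0.05, power = 0.80", with "64% success in the SHAM group" and "79% success in the SENS-U group, 124 children per group are needed". Allowing for 23% loss, this becomes 160 per group, or 480 in three arms.

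Two qualifications follow, neither with a figure. On using proportions in place of counts: "This will give a slight overestimation of the necessary sample size when analyzing wetting accidents per week, since this latter variable has more variance". On sidedness: "The one-sided alpha will provide a slight underestimation of the sample size". The section then concludes: "we presume that the overestimation and underestimation will cancel each other out".

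The section Data analysis and publication plans a Poisson or linear mixed model for the primary outcome, using all time points, and does not state the sidedness of the test.

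**The concern.** This is the article's only power statement for the primary comparison. The remark that a one-sided alpha understates the sample size makes sense only against a stricter benchmark, in practice a two-sided 5% test. If the final test were one-sided at 5%, there would be nothing to understate. The authors therefore concede a shortfall, call it slight, and remove it by setting a second unquantified error against it. The reason given for that second error also runs against the conclusion drawn from it.

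What is at stake is how a null result is read. A non-significant SENS-U versus SHAM comparison would be judged against 80% power. On the protocol's own responder assumptions and two-sided testing, the chance of missing the assumed effect is nearer 30% than 20%. For the count model that will actually be used, no power is known.

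**Working it through.** **Inputs (Sample size section):** p1 = 0.64 (SHAM), p2 = 0.79 (SENS-U), difference d = 0.15, alpha = 0.05, power = 0.80, equal groups, 124 evaluable and 160 enrolled per group.

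**1. Reproduce the stated 124.** The uncorrected formula is

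n0 = [z(alpha) × √(2·p̄·q̄) + z(power) × √(p1·q1 + p2·q2)]² / d²

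with p̄ = 0.715, 2·p̄·q̄ = 0.40755 and p1·q1 + p2·q2 = 0.2304 + 0.1659 = 0.3963.

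- One-sided: (1.645 × 0.6384 + 0.842 × 0.6295)² / 0.0225 = 110.9, i.e. 111.
- The continuity correction that approximates Fisher's test is n = (n0/4) × [1 + √(1 + 4/(n0·d))]². It gives 123.9, i.e. **124**, as stated.

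**2. The same calculation at two-sided 5%.**

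- Uncorrected: (1.960 × 0.6384 + 0.842 × 0.6295)² / 0.0225 = 141.0, i.e. 141.
- Continuity-corrected: 154.04, rounded up to **155**.

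**3. Exact Fisher power.** This sums the product of the two binomial probabilities over all outcome pairs with Fisher p ≤ 0.05.

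| Evaluable per group | One-sided 5% | Two-sided 5% |
|---|---|---|
| 123 | 80.2% | 69.9% |
| 124 | 80.6% | 70.4% |
| 152 | | 79.8% |
| 153 | | 80.04% |
| 155 | | 80.7% |
| 160 | | 82.1% |

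Two-sided 80% power therefore needs 153 (exact) to 155 (formula) per group. Since 153/124 = 1.23 and 155/124 = 1.25, the shortfall is 29 to 31 children per group, or 23% to 25%.

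**4. Direction of the stated reason.** For a difference in means δ with arm variances V1 and V2, n per group = (z(alpha) + z(power))² × (V1 + V2) / δ². At a given δ, more variance raises n. The reason offered therefore cannot support an overestimate.

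**5. Direction of the offset itself.** For cancellation, the two-sided count analysis would have to need no more than about 124 per group. The article gives no count distribution, so the following are assumptions (large-sample formulas, one time point, no baseline adjustment, 80% power).

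| Assumed mechanism | n per group, one-sided | n per group, two-sided |
|---|---|---|
| Latent normal shift matching 64% vs 79% (d = 0.448) | 62 | 79 |
| Negative binomial, zero-probability 64% vs 79%, common shape 0.1 to 5 | 28 to 95 | 35 to 121 |
| Effect only on the success probability; successes count 0; failures share mean and CV, CV = 0.5 | 149 | 188 |
| As above, CV = 1 | 266 | 338 |
| As above, CV = 1.5 | 462 | 586 |

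Example for CV = 1: the summed variance, in units of the squared failure mean, is 0.36 × 2 − 0.36² + 0.21 × 2 − 0.21² = 0.9663. Then 0.9663 × (1.645 + 0.842)² / 0.0225 gives 266 one-sided.

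In the first two rows, sizing on proportions does overestimate the number needed. In the last three it underestimates it. The sign is not determined by anything in the article.

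**The case against.** Four points can be made for the protocol.

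- **Sidedness is disclosed.** The article states one-sided alpha openly and says that it lowers the number. An article may leave the sidedness of the final test to an analysis plan that is not shown, so silence in the analysis section is not counted as a fault here. This stands. What remains is the size given to the shortfall and the claim that it is offset.
- **More than 124 may contribute.** The planned model uses all time points and the last available data of children who withdraw, so the effective number lies between 123 and 160. This also stands. Two-sided responder-scale power is properly given as a range of about 70% to 82%, with 70% at the article's own planned evaluable number.
- **Counts often carry more information than a dichotomy.** This is true, and the first two rows of the second table show it. A poor reason does not make the conclusion false. A reader might infer that the offset has the wrong sign and that the two errors add, or might quote one low simulated power for the count analysis. The documents do not support this. Such results require that benefit acts only by moving children from failure to success, and the conclusion reverses when the whole distribution shifts. The Sample size section does not define success as fully dry, and the Background counts up to one wet episode a week within its quoted success rate.
- **The loss allowance is not an error.** 124/0.77 = 161.04 might suggest that 160 is too few. But 124/160 = 0.775 is a 22.5% loss, printed as 23%, and 123 evaluable children still give 80.2% one-sided. This is rounding.

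**Conclusion.** Wrong as written. On the protocol's own proportions, the 80% belongs to a one-sided 5% Fisher test only. For two-sided 5% inference, which the underestimation remark implies but the article does not state, exact power is 70% at 123 to 124 evaluable per group and 82% at 160. The sample-size understatement is 23% to 25%, which is not slight. The offset presumed to cancel it has no figure and rests on a reason pointing the other way. Its true sign depends on an unknown count distribution.

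The Fisher figures rest only on the article's 64%, 79% and group sizes. The count scenarios rest on assumed distributions. They serve only to show that the sign can go either way, not to estimate the trial's power.

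**What to change.** In the Sample size section:

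1. Delete the argument that the two errors cancel, together with the more-variance reason.
2. State the sidedness of the primary test.
3. If it is two-sided 5%, restate responder-scale power as about 70% at the planned evaluable number, rising to 82% if all 160 per group contribute. If it is one-sided 5%, say that the 80% applies to that test only and remove the underestimation remark.
4. Report simulated power for the planned count mixed model under a stated range of count distributions. Include both a shift across all children and an effect confined to the probability of success.

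No extra enrolment is asked for, and neither treatment nor the planned analysis changes. The cost is a less favourable stated power and a short simulation.
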